### Confidentiality

The research teams will hold data according to the General Data Protection Regulation (May 2018). Each participant will be allocated a unique trial identification number, and on all trial-specific documents, other than the signed consent form, the participant will be referred to by the participant number, not by name. Only relevant members of the trial team will have access to participant personal information that will be stored on REDCap.

### Sample size

A previous meta-analysis of Randomised Controlled Trials (RCTs) examining work coordination programmes for work disability found an HR for time to RTW of 1.34 (95% CI: 1.14 to 1.56).^23^ With 90% power, 5% alpha, to detect an HR=1.34, assuming a median time to RTW of 3.2 months.^17^ Accounting for 20% attrition, an average of 31 patients per RTWC, intraclass correlation (ICC)=0.01 the sample size required is 742 with equal allocation. A minimum of 12 RTWC would be required to deliver the trial. The sample size was calculated for a log-rank test using PS power and Sample Size software.

### Data and statistical analysis

Statistical analyses will be on intention-to-treat (ITT) basis with patients being analysed in the groups to which they were randomised. Statistical significance will be at the 5% level and analyses will be conducted in the latest available version of Stata or similar statistical software.

Baseline characteristics will be reported descriptively by treatment group. Continuous data will be summarised as means, SD, medians and ranges and categorical data will be summarised as frequencies and percentages. No formal statistical comparisons of baseline data will be undertaken. Data will be visually inspected, and any imbalance reported.

### Primary outcome

The primary analysis will be an assessment of treatment differences evaluated using the Cox proportional hazard model with shared centre and RTWC frailty effects and adjusting for important baseline covariates (including stratification factors). The HR, CI and p value will be reported. Median time until full return to any work and Kaplan-Meier survival curves will be presented by the trial arms and a log-rank survival comparison will be made.

### Secondary outcomes

Time to any RTW will be analysed using a similar model to the primary analysis. Other secondary outcomes will be analysed using linear mixed models (eg, OKS/OHS), LEFS, PROMIS) or logistic regression (workplace intervention) as appropriate. For the number of sick days taken after surgery and before sustained RTW, a Poisson regression will be completed. Differences between allocated groups will be reported for all available time points.

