## Introduction

### Background and rationale

 In the UK, National Institute for health and Care Excellence (NICE) clinical guidance (NG157) recommends that orthopaedic teams discuss and provide information on return to work (RTW) for patients undergoing primary hip and knee replacement.^1^ Despite this, there is substantial variation in the provision of occupational advice and support.^2^ The current ‘standard of care’ is for patients to receive little or no information or support from their hospital orthopaedic team or General Practitioner (GP) to enable RTW.^3^,^6^ Furthermore, fewer than 35% of patients have access to occupational health support at work.^3^,^6^ There is a need for an occupational support intervention that encourages safe and sustained RTW and can be integrated into UK National Health Service (NHS) practice.

Planned surgery to replace a hip or knee joint is a routine NHS procedure that is becoming more common in people of working age. A quarter of UK patients undergoing primary hip and knee replacement are in work at the time of surgery (~50 000/year).^3 7 8^ This proportion will rise over the next decade with an increasing incidence of hip and knee osteoarthritis^9^ and people working longer.^10^ Returning to work is an important indicator of functional rehabilitation and quality of life. Working has physical and mental health benefits and aids recovery after joint replacement.^11^,^13^ Estimates for the mean time to RTW after hip or knee replacement range from 10 to 14 weeks.^314^,^17^ This equates to approximately 4.2 million days of sickness absence related to recovery after surgery at a societal cost of approximately £400 million/year.^3^

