#### Secondary outcomes

- Time to any RTW.

- Measures of functional recovery to daily activities and social participation:

Oxford Hip/Knee Score (OKS/OHS)^26 27^—joint-specific, PROMs designed to assess disability in patients undergoing hip (OHS) or knee (OKS) replacement. Each score contains 12 questions scored on a 5-point scale (0–4 points) producing scores ranging from 0 (poor function) to 48 (good function).Lower Extremity Functional Scale (LEFS)^28^—a valid self-reported patient-rated outcome for the measurement of general lower extremity function. It contains 20 questions each scored on a 5-point scale (0–4 points) producing scores ranging from 0 (very low function) to 80 (very high function). It has been shown to have good measurement properties compared with the SF36 and WOMAC scores^29^—WOMAC (Western Ontario and McMaster University Osteoarthritis Index) is disease specific for hip or knees and is scored by the patient. SF36 (Short Form 36 Health Survey Questionnaire) is used to indicate the health status of participant populations.PROMIS social participation short form questionnaires (eg, ability to participate questionnaire, satisfaction with social roles and activities questionnaire, satisfaction with participation in social roles questionnaire)^30 31^—PROMIS (Patient-Reported Outcomes Measurement Information System) is a set of person-centred measures that evaluates and monitors physical, mental and social health. We will use the social health tools developed by PROMIS to measure social participation and satisfaction with participation and social roles.

- Number of ‘sick days’ between surgery and ‘full’ sustained RTW.

- Participant adherence to the intervention and the intervention’s physical rehabilitation programme (including self-reported, 5-point Likert scales (very helpful, helpful, neither helpful nor unhelpful, unhelpful, very unhelpful)).

- Proportion of participants using workplace interventions, adaptations and modifications to facilitate their RTW (eg, changes in working hours and shift patterns, changes to work role or work environment or use of additional equipment within the workplace).

- Health-related quality of life (Euroqol 5 Dimensions 5 Levels (EQ-5D-5L)).^32^

- Work productivity (Work Limitations Questionnaire).^33 34^

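### Poisson regression for the number of sick days makes no allowance for overdispersion, so its confidence interval would be too narrow and its p value too small

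*Protocol article*

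**What the plan says.** The outcome is listed in the protocol article, Outcomes, Secondary outcomes, as: "Number of ‘sick days’ between surgery and ‘full’ sustained RTW". The analysis is fixed under Data and statistical analysis, Secondary outcomes: "For the number of sick days taken after surgery and before sustained RTW, a Poisson regression will be completed". That sentence has no qualifier. The wording that leaves some choice to the analyst belongs to the sentence before it, on linear mixed and logistic models. No dispersion term, robust variance, negative binomial alternative or clustering is mentioned for the sick-days model, whereas the primary Cox model has frailty terms for centre and RTW coordinator.

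The general rule for testing is: "Statistical significance will be at the 5% level". On the size of the counts, Background and rationale says: "Estimates for the mean time to RTW after hip or knee replacement range from 10 to 14 weeks". The same section puts sickness absence at about 4.2 million days a year among about 50 000 working patients.

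**The concern.** A Poisson model suits counts of separate, roughly independent events. Sick days after joint replacement are different: one operation starts one long absence, and each person's count is mainly the length of that absence. Lengths differ between people by far more than the square root of their mean, particularly in a trial that takes paid and unpaid workers in any job, hip and knee patients together, and follows them for up to 12 months.

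When the variance exceeds the mean, the Poisson rate ratio remains a usable estimate but its model-based standard error is too small. Either arm could then appear to have fewer sick days by chance alone. Sickness absence is the burden that the article uses to justify the trial, so such a result reported beside a null primary outcome could mislead.

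**Working it through.** **The plan's own figure.** The article gives no figure for the sick-days analysis. Its only calculated figure is the total of 742, from "With 90% power, 5% alpha, to detect an HR=1.34, assuming a median time to RTW of 3.2 months" and "Accounting for 20% attrition, an average of 31 patients per RTWC, intraclass correlation (ICC)=0.01 the sample size required is 742 with equal allocation".

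- Events needed (Schoenfeld): 4 × (1.960 + 1.282)² / (ln 1.34)² = 491.
- Assume exponential times over 12 months, with medians 3.2 and 3.2/1.34 = 2.39 months. Event probabilities are 0.926 and 0.969, average 0.9475. Then 491 / 0.9475 = 518, or 520 as 260 per arm.
- Design effect 1 + 30 × 0.01 = 1.30, in the intervention arm only, averages 1.15. The stated minimum of 12 coordinators supports this, since 12 × 31 = 372 is about one arm.
- 520 × 1.15 / 0.8 = 747.5, within 1% of 742.

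The number analysed is about 0.8 × 742 = 594, or 297 per arm.

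**What Poisson implies.** The stated mean of 10 to 14 weeks is 70 to 98 days. The absence figures give 4.2 million / 50 000 = 84 days per patient. The Poisson SD is the square root of the mean: 8.4 days at 70, 9.2 at 84 and 9.9 at 98.

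**Effect on the test.** Let φ = variance / mean. The true standard error is √φ times the Poisson one, and the actual two-sided error of a nominal 5% test is 2 × [1 − Φ(1.96/√φ)]. Sample size does not enter. The SD is an assumption, so a range is shown, at mean 84:

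| Assumed SD (days) | φ | SE too small by factor | False-positive rate |
|---|---|---|---|
| 15 | 2.7 | 1.6 | 23% |
| 20 | 4.8 | 2.2 | 37% |
| 25 | 7.4 | 2.7 | 47% |
| 30 | 10.7 | 3.3 | 55% |
| 40 | 19.0 | 4.4 | 65% |
| 60 | 42.9 | 6.5 | 76% |

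The rate passes 50% at φ = (1.960/0.674)² = 8.4, that is, at an SD of √(8.4 × 84), about 27 days.

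If sick days are counted as five in every seven calendar days, mean and SD both shrink by 5/7 and so does φ. The two ends of the table become φ = 1.9 and 30.6, with error rates of 16% and 72%.

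**Assumed time distributions with the 3.2-month median, capped at 365 days** (2000 simulated null trials each, 594 patients):

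- Exponential: mean 130, SD 109, standard error 9.6 times too small, false-positive rate 85% (84% by the formula). Counted as working days: mean 93, SD 78, factor 8.1, rate 81%.
- Weibull with shape 2, 3 and 4, calendar days: 72%, 60% and 48%.

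Simulated gamma counts at mean 84 with SD 15 to 40 agreed with the table to within about a percentage point. With robust standard errors the false-positive rate across all these runs lay between 4.0% and 5.7%.

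**Could an offset help?** RTW data are collected only until sustained RTW, so for those who return, observed time on this outcome is time to RTW, almost the same quantity as the count. Simulating a true hazard ratio of 1.34 gave a sick-day ratio of 0.78 (exponential) or 0.86 (Weibull shape 2) without an offset. With the log of time to RTW as offset, both became 1.00.

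**The case against.** The best defence is that naming Poisson regression does not fix the variance estimator. This is a condensed article, the analysis plan is not shown, and that plan may well specify robust or scaled standard errors; Poisson with a sandwich variance is still a Poisson regression. This stands as a limit: nobody can say that the final analysis will use model-based errors. It does not remove the point. The article names a model without qualification, and followed as written that model gives invalid intervals for this kind of count.

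Adjustment for covariates would absorb some of the spread, but from an SD of 30 days it would have to explain 1 − 84/900 = 91% of the variance before Poisson held.

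Several stronger readings are tempting and are not supported:

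- **That the outcome would come out significant most of the time with no true effect.** This needs an SD above about 27 days at mean 84, and the article gives none. At SDs of 15 to 25 days the rate is 23% to 47%.
- **That about 85% is the plan's own figure.** The article states a median, not a distribution. The exponential form is an assumption that reproduces 742 closely, but its mean of 130 days lies outside the article's 70 to 98.
- **That people who withdraw or are not back at 12 months enter with truncated counts treated as complete.** The article does not say so, and nothing above measures it. Their handling can properly sit in the analysis plan.
- **That this is a key secondary outcome.** It is one of several unranked secondary outcomes.

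**Conclusion.** The point holds for a Poisson model with its ordinary standard errors, which is the natural reading of the sentence. Standard errors would be about 1.6 to 6.5 times too small and the false-positive rate about 23% to 76% instead of 5%, for assumed SDs of 15 to 60 days at a mean of 84. Under the assumed exponential distribution the rate is about 85%.

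The direction does not depend on the exact SD, because any value well above about 9 days invalidates the test; only the size does. The mean is taken from background figures on time to RTW and total absence, not from trial data on sick days. The defect is confined to one secondary outcome and leaves the primary Cox analysis as it is.

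**What to change.** Replace the sentence with one to this effect: the number of sick days will be analysed by Poisson regression with robust (sandwich) standard errors, or by negative binomial regression, adjusted for joint (the stratification factor) and allowing for clustering by RTW coordinator in line with the primary model.

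Two cautions apply. Do not use time from surgery to RTW as an offset, for the reason shown in the working. And the simulations tested robust standard errors without clustering; neither the clustered form nor the negative binomial model was run. With a stated minimum of 12 coordinators, all serving one arm, the analysis plan should say how the small number of clusters is handled.

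The change needs no new data and no change to the sample size. Its cost is a wider confidence interval for this outcome.

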### Process evaluation

A mixed-methods process evaluation will be used to assess the intervention using a revised version of the Carroll *et al*^35^ conceptual framework for implementation fidelity. To inform how the trial findings could be incorporated into developments in service delivery/future implementation, we will draw on relevant data from across the qualitative components of the trial, including how the intervention was implemented across the trial sites. This will be summarised using normalisation process theory (NPT)^36^ and, together with the main trial findings on effectiveness and cost-effectiveness data, will be discussed at the second stage interviews with service leaders. Data will be used to develop an implementation strategy for future roll out across the NHS, if appropriate.

### Intervention fidelity and qualitative outcomes

The following data will be collected:

- Qualitative observations of the RTWC during an initial appointment.

- An intervention delivery checklist was completed for all trial participants.

- Participant outcome questionnaires (3, 6, 9 and 12 months) and self-reported adherence to the intervention.

- Completion rates of patient/rehabilitation workbooks.

- Qualitative interviews with trial participants from the intervention arm.

- Qualitative interviews with trial participants’ employers.

- Qualitative interviews with RTWCs at the start and end of the intervention period.

- Qualitative interviews with the service leaders at the start and end of the intervention period.

Qualitative sampling will be purposive to achieve maximum variation^37^ and adequate information power.^38^

We will use NVivo software to assist qualitative data organisation and coding. We will conduct a framework analysis (using broad categories as described in the implementation fidelity model and the key characteristics of NPT) to summarise findings according to key trial outcomes: intervention fidelity, acceptability of intervention, engagement with/adherence to the intervention and implementation.^39^ Descriptive statistics of the quantitative process evaluation data will be integrated with qualitative findings using a mixed method matrix. Where relevant these data will be integrated with appropriate quantitative data to provide a more complete picture.

### Economic evaluation

Enhancing evidence on the cost-effectiveness of occupational therapies is highlighted in both the 2007 and 2020 research priorities of the Royal College of Occupational Therapists.^40^ However, existing systematic reviews indicate a lack of studies in the literature that report on the cost-effectiveness of occupational therapies.^41^ A full economic evaluation will be conducted alongside the OPAL trial to assess the cost-effectiveness of the OPAL intervention versus usual care over a 12-month period. The base case analysis will be performed from an NHS and personal social services perspective and follow the principle of ITT. A secondary analysis will explore the wider societal perspective.

Cost estimates for the intervention will incorporate the cost of all associated resources and materials required for its development, training and delivery. Resource use questions in the follow-up case report forms will capture participants’ healthcare utilisation in relation to their replaced hip or knee across primary, secondary and community care settings. Unit costs, obtained from established national costing sources, will be applied to each resource use item to estimate the total cost per participant.^33 42^ For the secondary analysis, data on lost productivity will be collected using the Work Limitations Questionnaire.^33^

The primary health outcome measure in the economic evaluation is quality-adjusted life-year (QALY), which will be calculated based on data collected from the EQ-5D-5L questionnaire at baseline and at each follow-up.^32 43^ An incremental cost-effectiveness analysis will be conducted to compare the intervention with usual care. Incremental cost-effectiveness ratios (ICERs) will be calculated and assessed against NICE’s willingness to pay (WTP) thresholds of £20 000 to £30 000 per QALY.^44^ In addition, the incremental cost per missed workday averted will also be calculated.

Uncertainty around the calculated ICERs will be assessed using a non-parametric bootstrapping technique.^45^ The bootstrapping results will be used to generate cost-effectiveness acceptability curves to illustrate the probability of the OPAL intervention being cost-effective at different WTP thresholds.^46^ Rubin’s multiple imputation method will be adopted to handle missing data, assuming the data is missing at random.^47 48^ Sensitivity analyses will be conducted to explore the robustness of the cost-effectiveness findings. A health economic analysis plan will be developed prior to data analysis and will follow the latest NICE health technology evaluations manual.^44^

### Plans to give access to the full protocol, participant level-data and statistical code

This paper constitutes a complete representation of the trial protocol. The full protocol and related documents for the OPAL trial are available (insert where documents are kept, eg, National Institute for Health and Care Research (NIHR) website). Anonymised participant-level data may be requested from YTU after trial completion. The approval of any data requests is at the discretion of the chief investigator and YTU.

### Oversight and monitoring

The coordination of the OPAL trial will be managed by YTU in collaboration with the sponsor and chief investigator. The Trial Management Group (TMG) will monitor the day-to-day management of the trial.

A Trial Steering Committee (TSC) will monitor the progress of the trial, provide independent advice and the independent chair will make recommendations to the funder.

An independent Data Monitoring Committee (DMC) will monitor the data arising from the trial and make recommendations to the TSC about trial continuation based on ethical and safety considerations. The trial will also be monitored by the sponsor (South Tees NHS Foundation Trust) and a representative will be invited to attend the TMG, TSC and DMC.

### Adverse event reporting and harms

#### Adverse events

Adverse events are defined as any untoward medical occurrence (ie, any unfavourable and unintended sign, symptom or disease), experienced by a trial participant and which is temporarily associated with trial treatment (intervention or control) and is related to hip or knee replacement or to the trial intervention or control treatments.

For the OPAL trial, Adverse Events (AEs) will only be considered as related to the hip or knee replacement or to the trial intervention or control treatments if:

They occur during the inpatient stay (after randomisation) for the primary joint replacement.They occur in the same limb as the replaced joint.They are related to the anaesthetic, surgery, hospital admission, physiotherapy or radiographic assessment.They are thought to be related to the trial intervention, trial processes.

AEs will be collected from the point of randomisation onwards, up to the 12-month follow-up point. Events occurring before randomisation will not be recorded. Ongoing review of AEs will take place during monthly TMG meetings, discussed with the TSC and reported to the sponsor and research ethics committee in-line with their guidelines.

### Patient and public involvement

The trial has been developed with patient advisors who have had hip or knee arthritis and joint replacement surgery. A patient advisory group, along with public members who worked with us securing funding for the trial, will continue to be involved during the conduct of this trial, support the development of patient facing documents, advise on trial processes and suggest how best to report trial findings to the public and patients. There are two members of the patient and public involvement group that are co-applicants of the trial.

### Ethics and dissemination

Dissemination will focus on supporting the wider adoption and implementation of the intervention (if effective); the dissemination plan, developed at the outset of the trial will be amended as the results of the implementation substudy become available. An HTA monograph of the findings will be produced as well as publications in other peer-reviewed journals, regardless of the trial outcome.

We will produce lay summaries targeted at specific stakeholders, presentations at relevant professional society events and press releases through the collaborating NHS organisations, occupational health service and universities. A plain language summary will be disseminated to trial participants who have expressed an interest in hearing about the findings.

At the end of the trial, the intervention content will be made available through the NIHR HTA journals webpage, with an implementation plan/toolkit. Even if the intervention is not proven to be effective there may be individual elements that would be useful to healthcare professionals or patients. Data will be made available to allow for inclusion in future meta-analyses with studies of the same intervention in other trials.

This trial was approved by the West Midlands—Edgbaston Research Ethics Committee, Rec Reference 23/WM/0013.

